## Limitation of the Study:

## 16. Plan for Supervision and Monitoring:

The research team combines experience in epidemiology, global health, biostatistics, primary health care, type 2 diabetes, international research and health promotion. The supervisors have a long record of teaching and supervising at undergraduate, master and postgraduate levels, and they have the necessary expertise for this supervision obligation.

The PhD student will collect the primary data in Nepal, perform the analysis, and draft the three planned papers. The week to week supervision will be handled by [name] and [name], and during fieldwork by [name] and [name].

## 17. Plan for Data Management and Analysis:

All analyses will be intention to treat, i.e., without regard to the compliance of individuals within their allocated study arm and with clustering-effect. At first, the baseline and follow-up characteristics will be compared to detect significant differences using appropriate tests such as student t-tests for normally distributed variables and chi-squared tests for categorical variables. As randomization will be at the ward (cluster) level in the study, random-effects model will be used to account for clustering effect. In addition, sensitivity of findings will also be tested by completing a per protocol analysis with the complete data set. In the event that randomization does not control for differences between the intervention and wait-list control cluster on baseline characteristics, we will statistically control for those differences in subsequent analysis of program effects. The final outcome will be modeled by using multiple linear regression analysis. All statistical analyses will be carried out in STATA, version 12. Two-sided p values will be reported with a statistical significance level of <0.05.

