### **Sample size calculation for diabetic populations**

A lifestyle intervention study in a primary health care setting showed a mean reduction in fasting plasma glucose level by greater than 1 mmol/L after one year intervention in the diabetic population (18). Based on the standard deviation of mean reduction of fasting plasma glucose in the intervention arm of 2.1 (18), considering intraclass correlation of 0.01 and the design effect of 1.1 and 80% power into consideration, we will need 7 clusters with 11 individuals per intervention arm. To allow for the predicted dropout rate of 30%, the sample size was increased to 16 in each group i.e. 112 individuals per intervention group and the total sample size of the study will be 224.

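### Baseline fasting glucose should be a fixed covariate in the primary model; Section 17 ties adjustment to observed baseline differences and leaves open whether 12-month glucose or change is analysed

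*Protocol*

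**What the plan says.** Protocol Section 17 (Plan for Data Management and Analysis) starts by comparing baseline and follow-up characteristics with t-tests and chi-squared tests, looking for significant differences. It calls for a random-effects model to handle clustering by ward. Adjustment is then made conditional: "In the event that randomization does not control for differences between the intervention and wait-list control cluster on baseline characteristics", those differences are to be controlled for in the analysis of programme effects. On the model itself it says "The final outcome will be modeled by using multiple linear regression analysis". No covariate is named.

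The paragraph on sample size for diabetic populations (Section 15) works from a "mean reduction in fasting plasma glucose level by greater than 1 mmol/L after one year intervention in the diabetic population" and from the "standard deviation of mean reduction of fasting plasma glucose in the intervention arm of 2.1". That SD belongs to a change.

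The Study Variables entry gives the primary outcome only as mean fasting blood glucose. The Proposal Summary has participants measured at baseline and at 12 months. Under Sampling Methods, diabetes is defined by fasting capillary glucose of at least 7.0 mmol/l, so every trial participant has a baseline value.

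**The concern.** Two things are at stake.

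First, the set of covariates in the primary model is settled after looking at the data. The rule names no variables and no threshold, so different analysts could reach different primary models from the same data set. Baseline fasting glucose, the same measurement as the outcome taken a year before, enters only if the arms happen to differ on it.

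Second, the variance used for sizing is that of a change, while the analysed quantity is not fixed as change or 12-month value. If the unadjusted 12-month value is what gets analysed, its SD need not be 2.1, and the planned 80% power need not apply. Always adjusting for baseline settles both matters and needs no new data.

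**Working it through.** **Inputs from the protocol.** Difference 1 mmol/L and SD of the reduction 2.1; ICC 0.01, design effect 1.1 and power 80%; 30% dropout. The size before dropout is given as "we will need 7 clusters with 11 individuals per intervention arm". The sample-size paragraph gives no alpha, so it is taken from Section 17: "Two-sided p values will be reported with a statistical significance level of <0.05".

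**The plan's own figure.** Individually randomised n per arm = 2 × (1.96 + 0.84)² × 2.1² / 1² = 69.2, rounded up to 70. Design effect = 1 + (11 − 1) × 0.01 = 1.10. Then 70 × 1.1 = 77 = 7 × 11 evaluable per arm. Dropout: 11 / 0.7 = 15.7, so 16 per ward, 7 × 16 = 112 per arm and 224 in total. The stated size reproduces exactly. Normal-approximation power with 77 per arm and SD 2.1 is 80.4%.

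**Assumptions not in the documents.** The baseline-to-12-month correlation r, shown over 0.3 to 0.7; equal SDs at the two times; the design effect of 1.1 applied to all three analyses.

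**Formulas.** With equal SDs, Var(change) = 2 × SD² × (1 − r). Holding the SD of change at 2.1:
- SD of the 12-month value = 2.1 / √(2(1 − r)). It equals 2.1 only at r = 0.5, is larger above that and smaller below.
- Residual SD after baseline adjustment = that SD × √(1 − r²) = 2.1 × √((1 + r)/2).
- Standard error of the arm difference = SD × √(2 × 1.1 / 77) = 0.169 × SD.
- Power from a noncentral t with 12 df (14 wards less 2), noncentrality 1 / SE.

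| r | SD, 12-month value | SD, adjusted | Power, unadjusted 12-month value | Power, change score | Power, baseline always included | Same, 11 df |
|---|---|---|---|---|---|---|
| 0.3 | 1.775 | 1.693 | 86.4% | 73.5% | 89.3% | 88.8% |
| 0.5 | 2.100 | 1.819 | 73.5% | 73.5% | 84.7% | 84.1% |
| 0.7 | 2.711 | 1.936 | 51.9% | 73.5% | 80.1% | 79.4% |

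Example at r = 0.7: unadjusted SE = 0.169 × 2.711 = 0.458, noncentrality 2.18; adjusted SE = 0.169 × 1.936 = 0.327, noncentrality 3.06.

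The change score drops from 80.4% to 73.5% only because the reference moves from the normal to t on 12 df. That is a consequence of having 14 clusters, not of the adjustment rule.

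**The conditional rule.** The protocol gives no trigger, so p < 0.05 in an individual-level t-test of baseline glucose was assumed, with cluster means analysed and 20,000 simulated trials per setting. With no true baseline difference, the rule adjusted for glucose in about 6% of trials. Its power was 87%, 74% and 54% at r = 0.3, 0.5 and 0.7, close to never adjusting, against 89%, 84% and 80% when baseline was always included. Type I error under the rule was 5.0%, 4.5% and 3.5%, against 5.2%, 5.1% and 5.1% with fixed adjustment.

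**If 2.1 were the SD of the 12-month value instead.** Always adjusting would raise power (t on 12 df) from 73.5% to 77.4%, 84.7% and 95.1% at the same correlations.

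**The case against.** **The outcome may be a change.** The sentence "The final outcome will be modeled by using multiple linear regression analysis" can mean the trial endpoint in general, and the specific objective in Section 14.4 speaks of reducing blood glucose, which fits a change analysis and the SD of 2.1. This stands. A reader might infer that the planned variance certainly belongs to a different analysis from the planned one; the text does not establish that. What it establishes is that the choice is open.

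**The covariate list may sit in the SAP.** Multiple linear regression implies predictors, and Section 17 does not literally exclude baseline glucose when the arms look alike. That is fair as far as silence goes. But the conditional rule is written into the protocol, and it is the only statement there on how covariates enter. An SAP following it would inherit the trigger.

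**The gain depends on unknowns.** This stands. With unequal SDs (baseline SD = k times the 12-month SD), the point at which the 12-month SD passes the SD of change moves from r = 0.5 to r = k/2. Selecting participants at 7.0 mmol/l or above truncates baseline values, makes equal SDs doubtful and may lower r. At r = 0.3 the gain over the unadjusted 12-month value is only about 3 points.

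**No inflated error rate.** A reader might infer that choosing covariates from the data raises the false-positive rate. The simulation showed none; at r = 0.7 the rule was conservative. A reader might also put a figure on how often some baseline variable would differ by chance. The protocol gives neither the number of variables tested nor their dependence, so no such figure is supported.

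**Baseline comparison has a use here.** The Potential Biases section says participants are recruited after wards are allocated, so differences could be systematic. This stands as a reason to look at baseline, not as a reason to let the result choose the primary model.

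**Conclusion.** The point holds. Section 17 makes adjustment follow from observed differences and does not fix baseline fasting glucose as a covariate, although it is available for everyone. Whether 12-month glucose or change is analysed is also unsettled, against a sample size built on the SD of change.

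Over r = 0.3 to 0.7, fixed baseline adjustment has more power than either alternative: about 3, 11 and 28 points over the unadjusted 12-month value, and about 16, 11 and 7 points over the change score. This rests on an assumed r, equal SDs at both times, an SD of change of 2.1 and a common design effect of 1.1.

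The stated sample size is arithmetically correct, and the planned analysis is not invalid. The loss is in power and in a primary model left open to choice after the data are seen.

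**What to change.** In Section 17, name 12-month fasting glucose as the analysed outcome. Include baseline fasting glucose as a covariate in the primary random-effects model whatever imbalance is observed. Remove the imbalance trigger from the primary analysis. Adjust for other baseline variables only in a sensitivity analysis whose covariates are listed in advance. Baseline comparisons may stay as a check for recruitment bias, with a statement that they do not select the primary model.

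The cost is a few sentences; no extra data or participants are needed. At most one between-cluster degree of freedom is spent, which takes 0.5 to 0.7 power points (for example 80.1% to 79.4% at r = 0.7).

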## 18. Expected Outcome of the Research:

The perspective of this study is to develop and implement, in collaboration with the community people, community-based, culturally sensitive diabetes prevention and control programs. Monitoring blood glucose with point-of-care testing at home can diagnose as well as monitor how well diabetes is controlled. The project thus aims to reduce morbidity and mortality from type 2 diabetes through regular screening of blood glucose levels by mobilizing community health workers and establishing a referral system. Reducing blood glucose level may lead to a big impact on reducing morbidity and mortality from type 2 diabetes. It will further increase our knowledge on how to control blood sugar by mobilizing community health volunteers. Hence, the research output has the potential to bring immediate benefits to address non-communicable disease. At the same time, the project is highly interdisciplinary and combines culturally appropriate health education and health promotion approaches to diabetes education, engages and trains locally available FCHVs for non-communicable disease prevention including diabetes, as well as establishes local coalition whose focus is on increasing awareness and promoting healthy lifestyle changes. Involving local volunteers will help to address social, cultural, political, and economic systems to change health behaviors and outcomes of the community, which ultimately supports to place a high priority on transferring findings into new practices and policies. The assessment of FCHVs' skill may help to develop a policy that can be scaled-up to a national level. If the health promotion package is found effective, the approach can be easily adopted into the existing health care delivery system in Nepal. The research output can bring immediate benefits to the individuals of the intervention area as well as contribute to the development of a national diabetes management plan. Collaboration with the Ministry of Health and Population of Nepal is ensured already at the planning phase in order to stream-line the potential beneficial results of the project into policy with these regards. It is anticipated that the program can act as a feasible and affordable tool for evidence-based integrated care for improvement of diabetes management and outcomes in Nepal as well as in low- and middle-income countries elsewhere.

## 19. Plan for Dissemination of Research Results:

The Principal investigator will use this project as part of his PhD thesis. So, it will be disseminated in his unit at the university. Three manuscripts will be prepared together with co-investigators to publish in international peer-reviewed journals. In addition to this, the research will be disseminated at district level and national level by organizing workshops and seminars in collaboration with Ministry of Health and Population. Further, findings will also be disseminated through participation in several national and international conferences.

## 20. Plan for Utilization of the Research Findings (optional):

|  |
|--|
|  |
|--|

How is the research project going to strengthen the research capability of the host institution: Nepali Researcher (if submitted from abroad):

|                                                                                                                                                                                                                                                                                                                   |
|-------------------------------------------------------------------------------------------------------------------------------------------------------------------------------------------------------------------------------------------------------------------------------------------------------------------|
| The principal applicant is from Nepal. As a PhD student he will strengthen the research capability of himself through close supervision and guidance of the experts from Nepal and Denmark. He will engage in collaboration and mutual capacity-building with Nepali research colleagues of national institutions |
|-------------------------------------------------------------------------------------------------------------------------------------------------------------------------------------------------------------------------------------------------------------------------------------------------------------------|

510 21. Work Plan (should include duration of study, tentative date of starting the  
 511 project and work schedule / Gantt chart):

| Activities/month                 | 2016 |   |   |   |   |   |   |   |   |    |    |    | 2017 |   |   |   |   |   |   |   |   |    |    |    | 2018 |   |   |   |   |   |   |   |
|----------------------------------|------|---|---|---|---|---|---|---|---|----|----|----|------|---|---|---|---|---|---|---|---|----|----|----|------|---|---|---|---|---|---|---|
|                                  | 1    | 2 | 3 | 4 | 5 | 6 | 7 | 8 | 9 | 10 | 11 | 12 | 1    | 2 | 3 | 4 | 5 | 6 | 7 | 8 | 9 | 10 | 11 | 12 | 1    | 2 | 3 | 4 | 5 | 6 | 7 | 8 |
| Detail plan of protocol          |      |   |   |   |   |   |   |   |   |    |    |    |      |   |   |   |   |   |   |   |   |    |    |    |      |   |   |   |   |   |   |   |
| Literature/Fund search           |      |   |   |   |   |   |   |   |   |    |    |    |      |   |   |   |   |   |   |   |   |    |    |    |      |   |   |   |   |   |   |   |
| Office Set Up                    |      |   |   |   |   |   |   |   |   |    |    |    |      |   |   |   |   |   |   |   |   |    |    |    |      |   |   |   |   |   |   |   |
| Preparation of baseline survey   |      |   |   |   |   |   |   |   |   |    |    |    |      |   |   |   |   |   |   |   |   |    |    |    |      |   |   |   |   |   |   |   |
| Baseline survey                  |      |   |   |   |   |   |   |   |   |    |    |    |      |   |   |   |   |   |   |   |   |    |    |    |      |   |   |   |   |   |   |   |
| Data analysis of baseline survey |      |   |   |   |   |   |   |   |   |    |    |    |      |   |   |   |   |   |   |   |   |    |    |    |      |   |   |   |   |   |   |   |
| Design & test training materials |      |   |   |   |   |   |   |   |   |    |    |    |      |   |   |   |   |   |   |   |   |    |    |    |      |   |   |   |   |   |   |   |
| Training to FCHVs                |      |   |   |   |   |   |   |   |   |    |    |    |      |   |   |   |   |   |   |   |   |    |    |    |      |   |   |   |   |   |   |   |
| Intervention                     |      |   |   |   |   |   |   |   |   |    |    |    |      |   |   |   |   |   |   |   |   |    |    |    |      |   |   |   |   |   |   |   |
| Follow up survey                 |      |   |   |   |   |   |   |   |   |    |    |    |      |   |   |   |   |   |   |   |   |    |    |    |      |   |   |   |   |   |   |   |
| Dissemination                    |      |   |   |   |   |   |   |   |   |    |    |    |      |   |   |   |   |   |   |   |   |    |    |    |      |   |   |   |   |   |   |   |
| Report writing/publication       |      |   |   |   |   |   |   |   |   |    |    |    |      |   |   |   |   |   |   |   |   |    |    |    |      |   |   |   |   |   |   |   |
| Monitoring and supervision       |      |   |   |   |   |   |   |   |   |    |    |    |      |   |   |   |   |   |   |   |   |    |    |    |      |   |   |   |   |   |   |   |
| Project management               |      |   |   |   |   |   |   |   |   |    |    |    |      |   |   |   |   |   |   |   |   |    |    |    |      |   |   |   |   |   |   |   |

512

513

514

515

516

517

518

519

520

## Part – IV

### Ethical Consideration

22. Regarding the human participants:

Are human participants required in this research? If yes, provide justification.

☒

Yes (*provide justification*)

☐

No

How many participants are required for the research? Explain.

2643

What is the frequency of the participant's involvement in the research? Explain.

2

Clearly indicate the participant's responsibilities in the research. What is expected of the research participants during the research?

Participants will provide information and receive health information package in intervention VDCs

Are vulnerable members of the population required for this research? If yes, provide justification.

No

Are there any risks involved for the participants? If yes, identify clearly what are the expected risks for the human participants in the research and provide a justification for these risks.

No

Are there any benefits involved for the participants? If yes, identify clearly what are the expected benefits for the participants.

For the participants in the intervention VDCs, they will get an opportunity to measure their blood glucose level, blood pressure and receive health education package from FCHVs.

### 23. Informed Consent Form / Ethical Issues:

Statements required in the Informed Consent Form include:

A statement that the human participants can withdraw from the study at any time without giving reason and without fear. State clearly how the participants can opt out the study.

A statement guaranteeing the confidentiality of the research participants.

If required, a statement on any compensation that might be given to the research participant and or their community.

A statement indicating that the participants has understood all the information in the consent form and is willing to volunteer / participate in the research.

Signature space for the research participants, a witness, and the date.

*(Informed Consent form should be submitted in English and in the language appropriate to the research participants)*

#### Obtaining the Consent

How informed consent is obtained from the research participants?

☐

Verbal

☒

Written

Please indicate who is responsible for obtaining informed consent from the participants in this research study?

.....

Is there anything being withheld from the research participants at the time the informed consent is being sought?

If yes, explain

.....

Is the research sensitive to the Nepali culture and the social values?

Yes ☐ No ☒ Explain.

.....

Is health insurance (*if applicable*) being made available to the research participants? If yes, please provide the necessary insurance data.

.....

(Include in consent form)

#### 24. Regarding Clinical Trial:

In case of a clinical trial address the following:

The trial treatment

.....

A detailed explanation of the trial procedures including all invasive procedures.

.....

The potential or direct benefits (if any) for the research participants.

.....

Alternative procedure(s) or treatment(s) that may be available.

.....

The risks, discomforts, and inconveniences associated with the study

Infection and pain at blood sampling site

.....

Provisions for management of any adverse reactions

661  
662 To avoid these risks, a well-trained person will be hired to take the blood sample and hand  
663 hygiene will be performed  
664 .....  
665 The provisions of insurance coverage for any permanent disability or death  
666 caused directly by the investigational treatment or procedure.  
667 .....  
668  
669 The provision of including the name and address, including telephone  
670 numbers of person to be contacted in case of adverse events or for any  
671 information related to the trial.  
672 .....  
673  
674 Is there going to be a transfer of any biological materials from the country?  
675 Explain.  
676 .....  
677  
678 Is there a Data Safety Monitoring Board?  
679 If Yes, Mention  
680 .....  
681  
682 Is this trial internationally registered?  
683 .....  
684  
685  
686  
687  
688  
689  
690  
691  
692  
693  
694  
695  
696  
697  
698  
699  
700

**INFORMED CONSENT:**

- ⌚ Describe the manner in which informed consent will be obtained.
- ⌚ Indicate what kind of consent (e.g. parental, child, adult, etc) will be used.
- ⌚ If the subjects are children/adolescents ages 7-18 years, an Assent Form must be included with the IRB application. The signed Assent Form along with the Parental/Guardian Consent Form must be retained on file for at least three years after completion of the research project.
- ⌚ If prisoners / pregnant women, or fetuses are to be included in the research sample, it is likely that a full IRB review will be required and additional human subjects' protections will be expected.
- ⌚ If the subjects do not read or comprehend English, you must provide a consent form in their language as well as in English for IRB review and approval.
- ⌚ If you are requesting a waiver of written consent (i.e. a signature on an informed consent form) from the subjects, you **MUST** justify this request by providing an explanation of why obtaining written consent would add additional risk to the subjects and your alternative provisions for informing them about the study.
- ⌚ If consent documents from another site will be used, you will have to indicate this and provide a copy of the authorized consent document and IRB approval with your application.
- ⌚ You will have to provide any other relevant information if necessary. Please be aware that the PI is legally required to retain all signed Informed Consent forms for at least three years after the project terminates
- ⌚ The Informed Consent form must be written at a level that the subjects will understand. Please use simple language, and avoid clinical jargon.
- ⌚ Attach a copy of the written informed consent form (assent or parental consent where applicable). Consent documents **MUST** be in format requested. See examples on line.
- ⌚ If the study uses database or archival data the use of informed consent is not applicable.

